##### Motor and Gait Assessment

Behavioral assessment of each PD participant will be conducted on three occasions, before and after a 10-week exercise program, and at a 6-month follow-up time period. Healthy control participants will be assessed at time 1 only. PD participants will initially be assessed with the Part-III (motor) section of the Movement Disorder Society—Unified Parkinson Disease Rating Scale [MDS-UPDRS (Goetz et al., 2008)]. Assessment of gait function under single-task (walk only) and DT conditions will be conducted on a treadmill, instrumented with a pressure mapping system. Treadmill walking is used to obtain 40–60 consecutive steps and at a constant speed [see Bhatt (2018) and Szturm et al. (2017) for a detailed description of data recording, analysis, and test-retest reliability]. Participants will be instructed to walk on the treadmill at their preferred gait speed without hand support for four 1-min intervals (one single-task walking only, one VMT, and two VCG trials, described below). The center-of-pressure of foot displacement in the mediolateral (ML) and anteroposterior (AP) directions will be collected at 100 Hz.

A custom computer application with the following two assessment modules will be used for the DT test conditions: (a) a visuomotor tracking (VMT) task and (b) a visuospatial cognitive game (VCG) task. Figure 2 illustrates the gaming set-up for the VMT and VCG tasks. As described previously (Nankar et al., 2017; Szturm et al., 2017; Ahmadi et al., 2019; Mahana et al., 2021), an IB-mouse will be used to control and interact with the cognitive assessment games. The VMT task used in the present study requires real-time, on-line visual feedback of the relative positions of two objects. The VCG task requires visual search to locate target objects and cognitive inhibition to avoid distractors. The VMT and VCG tasks require precision head-pointing movement. Many real-life tasks involve head movements to track and locate various objects, and for information processing of what are being seen. The increased visuospatial processing necessary to maintain walking rhythm and to correct for any drifting on the treadmill would compete for resources required to perform the VMT and VCG tasks, and vice versa.

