
##### Neuropsychological Tests

Parkinson’s disease has been associated with cognitive impairment across a range of domains, including aspects of cognitive flexibility, inhibitory control, sustained attention, and working memory (Owen et al., 1993; Uekermann et al., 2003; Kudlicka et al., 2011; Weintraub et al., 2018). The Cambridge Neuropsychological Test Automated Battery (CANTAB) for PD will be used for assessment of cognitive function. These will include; (a) Paired Associates Learning, (b) Pattern Recognition Memory, (c) One Touch Stockings of Cambridge, (d) Spatial Working Memory, and (e) Match to Sample Visual Search. Health-related quality of life will be assessed with the PD Questionnaire (Damiano et al., 1999). This neuropsychological data will be collected prior to participation commencement, at the end of the 10-week intervention, and at a 6-month follow-up, in the same session as the other behavioral assessments.

Fall rate will be recorded for a period of 1-year after completion of the exercise program. Falls rates will be considered a secondary outcome, due to concerns about the reliability and validity of self-report falls diary data. A fall will be defined as an unexpected event in which the participant comes to rest on the ground, or the floor (Mirelman et al., 2016). Several options will be used for the recording of fall events and to maximize the accuracy of reporting. Participants will receive fall calendars, either a paper version, a web-based calendar, or a smartphone application. Information logged in the online or smartphone-based calendars will automatically be uploaded to a database. Participants will be provided pre-addressed envelopes, and will be instructed to mail the paper version once every month. If a fall is recorded, the participant will be contacted by their treating therapist and asked when and how the fall occurred and whether there was any injury or need for medical treatment.

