##### Physical Activity Tracking

In the second week of the exercise, program participants will be given a Fitbit watch (Ionic) to track physical activity levels during waking hours (Liang et al., 2018; Tedesco et al., 2019; Fuller et al., 2020). This model records steps taken, GPS and heart rate. Participants will be shown how to use the watch and how to access and transfer the stored data. Recorded activity data from the watch will be transferred to the therapist once a week during a treatment session. Over a 10-week time period this will provide ample practice on how to use the Fitbit watch and how to access and transfer its recorded activity data. Following the 10-week exercise program, the participants will be shown how to transfer their activity data to the research team. They will be instructed to do this once a week. Participants will be sent an e-mail or text message to remind them to do so.

Walks of more than 1 min will be determined by data showing continuous steps and where there are concurrent and adequate changes in GPS and increased heart rate. For each walking bout exceeding 1 min, the walking distance will be determined using the GPS data. The main physical activity outcome measures will be the total monthly walking duration and walking distance. Walking speed will also be computed for each walking bout over 1 min, and a monthly average obtained. Following the exercise program, all participants will be contacted by phone once a month to remind them of the use of the physical activity tracker.

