#### Statistical Analyses

Our sample size was calculated based on our previous work involving PET imaging in PD in which participants were randomized into either gene therapy or sham-surgery groups, and assessed at 6 months follow-up (Ko et al., 2014a). With anticipated ρ2 = 0.673 [20% more than what is expected for placebo effect-related pattern’s explanation of clinical benefits induced by sham surgery over 6-months (Ko et al., 2014a)], G^∗^Power (version 3.1.9.2; RRID:SCR_013726) estimates the minimal sample size to be 12 (effect size f2 = 2.060). With maximally anticipated drop-out rate of 10% (e.g., motion artifacts, patient’s voluntary withdrawal, etc.); we require 13 subjects per group/site.

MATLAB (The Math Works Inc., Natick, MA, United States version 2010a) will be used to compute the outcome measures. Normality of the data will be assessed using the Shapiro-Wilks test. Sphericity will be assessed using Mauchly’s test. For normally distributed data sets, a mixed-model ANOVA will be used to examine the effects of time (pre– and post-intervention), group (XG and CG) and interaction of time^∗^group of all behavioral outcome measures (gait, cognitive, neuropsychological, fall rates, physical activity levels, and health-related quality of life). Note the time factor for fall rates, physical activity outcome measures, and health-related quality of life will include the 6-month and 12-month follow-up time periods. Non-normally distributed data will be assessed using the Wilcoxon-Signed rank test to determine differences between pre- and post-intervention. The significance level will be set at *p* < 0.05, and statistical analysis will be conducted using SPSS (v.22; SPSS Science, Chicago, IL, United States).

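### The time levels set for the behavioural analyses do not match when falls, activity, quality of life, gait and cognition are described as being collected

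*Protocol article*

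**What the plan says.** The Statistical Analyses section states the general model for behavioural outcomes: "a mixed-model ANOVA will be used to examine the effects of time (pre– and post-intervention), group (XG and CG) and interaction". The outcomes it lists are gait, cognitive and neuropsychological measures, fall rates, physical activity and health-related quality of life. It then makes an exception for three of them: "Note the time factor for fall rates, physical activity outcome measures, and health-related quality of life will include the 6-month and 12-month follow-up". The ANOVA is reserved for data that pass a Shapiro-Wilk check. For the rest, "Non-normally distributed data will be assessed using the Wilcoxon-Signed rank test to determine differences between pre- and post-intervention".

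The collection times are given in other sections:

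- Falls (Neuropsychological Tests): "Fall rate will be recorded for a period of 1-year after completion of the exercise program". The Figure 1 legend instead says that fall history and activity tracking run throughout the study, up to 12 months after the intervention. It does not say when they start.
- Activity (Physical Activity Tracking): "In the second week of the exercise, program participants will be given a Fitbit watch". The Behavioral Testing section continues tracking for 12 months after treatment.
- Quality of life and the cognitive battery (Neuropsychological Tests): before participation starts, then "at the end of the 10-week intervention, and at a 6-month follow-up, in the same session as the other behavioral assessments".
- Gait and motor assessment of PD participants (Motor and Gait Assessment): "will be conducted on three occasions, before and after a 10-week exercise program, and at a 6-month follow-up time period".

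**The concern.** A repeated-measures model needs data at each level of its time factor, and it tests nothing at a visit that is not one of its levels. Here the levels and the visits were set in different sections and do not agree.

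If the section is followed literally, the analyst has no described pre value for falls. For activity, the temptation is to let an on-treatment value stand in as baseline, which would absorb any change that occurred before the watch was issued. For quality of life, one planned level has no data behind it. For gait and cognition, data that bear directly on whether a benefit lasts are collected without a prespecified comparison of the arms.

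Each gap would have to be filled by a choice made after data exist. This is not detail that an article may leave to an unseen analysis plan, because the article fixes the time levels itself.

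**Working it through.** No sample-size or power figure in the article bears on this point, so the check sets planned levels against described collection, outcome by outcome.

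| Outcome | Planned levels | Described collection | Mismatch |
|---|---|---|---|
| Fall rate | pre, post, 6 m, 12 m | count over the 12 months after the program; legend suggests a wider window | no described pre value; no separate immediate-post value |
| Activity | pre, post, 6 m, 12 m | from week 2 of 10 to 12 m after treatment | no untreated value |
| Quality of life | pre, post, 6 m, 12 m | baseline, end of training, 6 m | 12 m has no described data |
| Gait | pre, post | pre, post, 6 m | 6 m not in the model |
| Cognitive battery | pre, post | pre, post, 6 m | 6 m not in the model |

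Five of five outcome groups mismatch: three have a planned level without described data, and two have a collected visit outside the model.

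**Which test falls would reach.** The article gives no fall rate, so this step uses assumptions. Take negative binomial counts with a mean of 3 to 5 falls a year in the control arm, size parameter 0.7 to 1, a rate ratio of 1 or 0.4, and 24 participants per arm (52/2 = 26 per arm; 26 × 0.9 = 23.4 after the article's 10% drop-out, rounded up). In simulation, Shapiro-Wilk applied to the pooled counts rejects normality at the 5% level in 99.5% to 100% of trials. Under these assumptions the plan's own rule almost always sends falls to the signed-rank test. That test has two problems here:

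1. It needs a paired pre value, and none is described for falls.
2. It compares time points within participants. It does not compare the experimental arm (XG) with the control arm (CG), which is the question of a randomised trial.

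**Effect of the same fallback elsewhere.** If activity or quality-of-life data fail the normality check, the fallback covers pre and post only. The follow-up levels that the same section has just added then drop out again.

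**The case against.** Several points on the other side are fair, and they limit what can be claimed.

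- **A reader might infer that no pre-intervention falls data exist.** The documents do not support that. The Figure 1 legend speaks of fall history acquired throughout, which could include a history taken at baseline, and the figure itself is not available. What stands is that no section describes such a measure, that the text defines fall rate as a post-program quantity, and that the passages disagree.
- **A reader might infer that the falls and activity analyses cannot be run.** That is too strong. A comparison of the arms over post-program periods is feasible for both. Only the literal pre level fails.
- **A reader might infer that the 6-month gait and cognition data will never be used.** The section omits them from the stated time factor; it does not exclude them. The Anticipated and Preliminary Results section expects better white-matter integrity to go with better gait stability and fewer falls at 6 months, which may draw on 6-month gait data. That is an association, however, and not a test of XG against CG. Nor would all 52 participants be expected at 6 months, since the article allows for 10% drop-out.
- **A reader might want to put a power loss on analysing raw fall counts by ANOVA.** That would mislead. The rates and effect would be assumed, and the plan's normality check would rarely select that ANOVA.
- **Importance.** The article makes falls secondary because of doubts about diary data, and its sample size rests on PET imaging, which this point does not touch.

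None of this removes the mismatches for activity and quality of life, the omission for gait and cognition, or the failure of the fallback to compare the arms.

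**Conclusion.** The point holds as an internal inconsistency between the analysis section and the collection sections. Its size is five of five outcome groups with at least one mismatched time level. The quality-of-life, gait and cognition parts follow from the text alone. The activity part rests on the week-2 issue of the watch, which rules out an untreated value from that device. The falls part is a conflict between the Figure 1 legend, the Neuropsychological Tests section and the Statistical Analyses section. Its practical consequence, a pre-post test with no described pre value and no comparison of the arms, also assumes that fall counts will be skewed.

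This should be corrected before analysis. It is not a fatal flaw: it leaves the PET-based sample size alone, and workable analyses exist with the data already planned.

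**What to change.** Rewrite the time levels in the Statistical Analyses section so that each outcome has its own set:

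- **Falls.** Compare XG with CG over the post-program year with a count model and no pre level. Negative binomial regression with log follow-up time as offset would serve, with a likelihood-ratio or permutation p-value because the sample is small. State in the Figure 1 legend and in the text when falls recording starts. Use a baseline fall history as a covariate only if one is in fact collected.
- **Activity.** Compare post-program monthly activity by arm and make no pre-post claim. Issuing the watch before training would give a true baseline, but this is optional and changes procedure: during training the data are handed over at weekly treatment sessions, so another transfer route would be needed.
- **Quality of life.** Set the time factor to baseline, post and 6 months.
- **Gait and cognition.** Add the 6-month visit to the model, with the between-arm contrast at post first and at 6 months second.

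Apart from the optional earlier watch, the cost is analysis wording and a clarified figure legend. No extra visit, participant or measurement is needed.

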A treadmill was chosen for the DT gait and cognitive functions for the following reasons. First, treadmill walking was chosen to overcome the confounding effect of gait speed. The treadmill allows the speed to be kept constant between walking conditions (single-task and DT), and over repeated measures (pre- and post-intervention time periods). This is of particular importance to standardize the uptake period of the PET imaging analysis at the three test periods. Most DT gait studies are performed overground, and all overground studies report a significant decrease in gait speed during the DT-walking condition, as compared to walk-only trials (Stegemöller et al., 2014; Raffegeau et al., 2019). Therefore, during overground DT-walking trials, there is a planned strategy to reduce the physical demands or threat to balance. Besides gait speed, many DT gait studies examine how cognitive demands affect gait rhythm and stability [i.e., recording spatiotemporal gait variables or analysis of trunk linear acceleration (Ijmker and Lamoth, 2012; Montero-Odasso et al., 2012; Asai et al., 2013; Martinez-Martin et al., 2013; Nankar et al., 2017; Ahmadi et al., 2019)]. However, gait speed is a confounding variable, as spatiotemporal gait variables and trunk acceleration are sensitive to changes in gait speed (Frenkel-Toledo et al., 2005; Jordan et al., 2007; Kang and Dingwell, 2008; Keene et al., 2016; Cole et al., 2017). Most overground DT-walking studies use an instrumented walkway, which records only 4–6 consecutive steps. It has been shown that using a continuous walking protocol, instead of short intermittent walks, and collecting more than 30 consecutive steps improved reliability, in particular for measures of gait variability and during DT-walking trials (Bruijn et al., 2009; Hollman et al., 2010; Galna et al., 2013). In addition, there is a limited choice of executive cognitive tasks that can be assessed during the short time period to walk a few meters. For example, cognitive tasks used during overground walking include walking while talking, recall of names/words, serial subtraction, or auditory Stroop (Stegemöller et al., 2014; Gregory et al., 2017; Ghanavati et al., 2018; Raffegeau et al., 2019; Snir et al., 2019). The present study extends these assessments to include visuomotor and visuospatial cognitive tasks assessed over a 1-min time period. Tracking visual objects and processing of what is being seen are important cognitive functions to consider in the analysis of DT interference on mobility (Nagamatsu et al., 2009; Logan et al., 2010). Cortical areas devoted to visual spatial ability such as the frontal and parietal lobes may be particularly susceptible to the neurodegenerative process of PD (Battisto et al., 2018; Lally et al., 2020). Following the principle of neural overlap (Crockett et al., 2017), DT interference should be greatest when the cognitive and motor tasks engage the same neural circuits and processing resources, e.g., visual-spatial processing. Walking endurance will be evaluated with a 6-min walk test [6MWT (Combs et al., 2014)]. Overground walking speed will also be evaluated over 25 m in a straight corridor.

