For the neuroimaging data, Aim 1 will use PET data to compare levels of metabolic activity by region between; (a) single-walk only and DT-walk trials, and (b) PD and able-bodied age-matched controls. Aim 2 will use PET and MRI (RS-fMRI, pCASL, and DTI) data to investigate neural changes (whole-brain and ROIs) between pre- and post-intervention. See Table 1 for the ROIs to be used in the PET and RS-fMRI data for Aims 1 and 2. Paired sample *t*-tests will be conducted for these different neuroimaging modalities, with age and gender included as regressors of no interest. Additional correlational analyses are planned to investigate the relationship between changes in neural activity and behavioral metrics such as cognitive task performance and gait measures.

**TABLE 1 T1:** Regions of interest for the PET and fMRI ROI analyses.

**Amygdala, L**	**Dorsolateral PFC, L**	**Inferior Temporal, R**	**Mesial Temporal, L**	**Orbital frontal, R**	**Thalamus, R**
Amygdala, R	Dorsolateral PFC, R	Insula, L	Mesial Temporal, R	Putamen, L	Uncus, L
Anterior Cingulate, L	Frontal pole, L	Insula, R	Midbrain	Putamen, R	Uncus, R
Anterior Cingulate, R	Frontal pole, R	Lateral Temporal, L	Middle Temporal, L	Substantia nigra	Ventral Striatum, L
Subgenual cingulate (BA 25)	Hippocampus, L	Lateral Temporal, R	Middle Temporal, R	Superior Temporal, L	Ventral Striatum, R
Caudate, L	Hippocampus, R	Medial PFC, L	Occipital	Superior Temporal, R	Ventrolateral PFC, L
Caudate, R	Inferior Temporal, L	Medial PFC, R	Orbital frontal, L	Thalamus, L	Ventrolateral PFC, R

*L, left; R, right; PFC, prefrontal cortex.*

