## Anticipated and Preliminary Results

The anticipated results of this study can be broken down by objective. First, in comparing if and how metabolic brain activity differs during single and DT-walking in PD patients, compared to able-bodied controls, we will likely observe increased activation of sensorimotor and cerebellar brain regions and decreased activation in the PFC of the PD patients. We hypothesize that these changes in brain activation patterns will be associated with decreased gait and cognitive performance measures and the magnitude of DT effects. Second, we hypothesize that both training programs will result in significant improvements in gate and cognitive function with medium to large effect sizes, and that the DT training program will result in significantly greater improvements in the XG compared to CG, also with medium to large effect sizes. It is hypothesized that the DT treadmill-training program will result in specific and significant changes of the DT gait-related abnormal brain metabolic pattern observed in Objective 1.

Our behavioral and PET hypotheses are supported by a recent feasibility study that we completed in which 15 PD patients (Hoehn and Yahr stages II-III) participated in a 10-week DT-treadmill gait training program using the VMT and VCG as described in the “Methods” section above (Mahana et al., 2021). Significant improvements in the majority of gait variables (average and COV of SL and SW) with medium to large effect sizes were observed following the intervention. This was the case for both walk-only and DT-walking assessments. There were also significant improvements in VMT and VCG outcome measures post-intervention with medium to large effect sizes. This was the case when tested while sitting and while treadmill walking. In addition, a qualitative analysis of the participant’s experiences revealed that the program was challenging and required a high degree of mental processing. The majority of participants reported that the games were engaging and they appreciated the variety of games used for the DT training. Also, to note 3 of the 15 participants did not like playing the games.

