In a recent pilot study, we tested the feasibility of imaging the DT-walking-related changes in brain glucose metabolism in patients with PD (Szturm et al., 2020). Fifteen patients with PD (stage II and III) were scanned with FDG-PET. Ten patients were rested during the FDG uptake period and five patients performed DT treadmill walking for 28 min. All five PD patients receiving the DT-walking protocol showed a consistent DT interference of gait measures (average and COV) and of all VMT and VCG performance measures. Glucose metabolism was significantly increased in several brain regions of the patients who performed the DT treadmill walking as compared to those who rested during the uptake period. These regions include primary visual/sensorimotor areas, thalamus, superior colliculus, and cerebellum. When individual results were analyzed, patients in the earlier stage of PD (Hoehn and Yahr stage II) showed increased FDG uptake in the PFC regions during DT treadmill walking as compared to resting levels. More progressed PD patients (Hoehn and Yahr stage III) did not show any notable increase in PFC activity during DT treadmill walking. It should be also noted that patients with mild cognitive impairment (MCI) also show suppressed PFC activity during walking (Holtzer and Izzetoglu, 2020).

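### None of the 42 regions in Table 1 is cerebellar or sensorimotor cortex, so the Aim 1 regional PET comparison can test only the prefrontal half of the direction the protocol predicts

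*Protocol article*

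**What the plan says.** Three parts of the protocol article bear on this.

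- **Statistical Analyses, Aim 1.** The neuroimaging paragraph opens: "Aim 1 will use PET data to compare levels of metabolic activity by region between". The two contrasts are single-task against dual-task (DT) walking, and PD against age-matched controls. It then gives the regions: "See Table 1 for the ROIs to be used in the PET and RS-fMRI data for Aims 1 and 2". The table is titled "Regions of interest for the PET and fMRI ROI analyses" and reads as a closed list. For Aim 2 the same paragraph is wider: the data will be used to "investigate neural changes (whole-brain and ROIs) between pre- and post-intervention".
- **Anticipated and Preliminary Results.** For the PD-versus-control comparison the authors write that "we will likely observe increased activation of sensorimotor and cerebellar brain regions and decreased activation in the PFC of the PD patients". They go on to hypothesise that these changes relate to gait and cognitive performance and to the size of the DT effects. They also expect training to alter the abnormal pattern found under Objective 1.
- **Objectives.** The formal hypothesis for Objective 1 expects metabolic differences in a number of cortical and subcortical areas and names none.

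**The concern.** The only place where Objective 1 is given a direction names three territories: sensorimotor regions and cerebellum (higher in PD) and PFC (lower in PD). The only region list given for the Aim 1 comparison appears to cover just one of them.

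Two things are at stake. First, the predicted increases are the evidence for greater recruitment in PD, and the Abstract says that the control comparison should find areas of excess as well as reduced activity. A regional analysis confined to Table 1 would report on the predicted decrease and be silent on the predicted increases. Second, if cerebellar or sensorimotor regions were added after the scans had been looked at, a positive result there would be post hoc although the article had predicted it.

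**Working it through.** No figure in the plan needs reproducing. The check is to read Table 1 entry by entry and set it beside the prediction.

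**Count.** Seven rows by six columns give 7 × 6 = 42 entries, all distinct. Nineteen structures have a left and a right entry and four have one (subgenual cingulate, midbrain, occipital, substantia nigra): 19 × 2 + 4 = 42 entries, 19 + 4 = 23 structures.

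**Composition.**

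| Group | Entries |
|---|---|
| Labelled PFC (dorsolateral, medial, ventrolateral) | 6 |
| Frontal pole, orbital frontal | 4 |
| Cingulate (anterior, subgenual) | 3 |
| Insula | 2 |
| Temporal cortex | 10 |
| Amygdala, hippocampus, uncus | 6 |
| Caudate, putamen, ventral striatum | 6 |
| Thalamus | 2 |
| Midbrain, substantia nigra | 2 |
| Occipital | 1 |
| **Total** | **42** |

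**Prediction against list.**

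| Territory | Predicted in PD vs controls | Entries in Table 1 |
|---|---|---|
| PFC | lower | 6 labelled as such (10 with frontal pole and orbital frontal) |
| Sensorimotor cortex | higher | 0 |
| Cerebellum | higher | 0 |

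The table has no label for motor, premotor, precentral, postcentral, supplementary motor, somatosensory or cerebellar tissue.

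**Could a listed region stand in?** Putamen and thalamus belong to motor circuits, but the article does not use sensorimotor in that sense. Its pilot summary names thalamus separately from the sensorimotor areas: "These regions include primary visual/sensorimotor areas, thalamus, superior colliculus, and cerebellum".

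**Does another stated analysis make the same test?** The FDG-PET Analysis section applies a whole-brain mask and ordinal trend/canonical variate analysis. Its patterns are derived from DT against single-task walking within controls, the same contrast within PD patients before training, and post- against pre-intervention DT walking. Every scan then receives a pattern score, and the topographies are compared for similarity. Cerebellum and sensorimotor cortex can load on these patterns. However, a network score or a similarity test does not say whether cerebellar or sensorimotor metabolism is higher in PD than in controls. In the Statistical Analyses paragraph, whole-brain analysis is stated for Aim 2 only.

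**The case against.** The strongest reply is that the sensorimotor and cerebellar wording is a forecast in the anticipated results, not the formal hypothesis, and that PET analysis is not confined to regions of interest. Both statements are correct, and they limit the point. Several stronger readings are tempting, and the documents do not support them.

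- *That the trial cannot test its Objective 1 hypothesis.* The hypothesis under Objectives names no region and can be tested with Table 1.
- *That the predicted increases cannot appear anywhere.* The whole-brain pattern analysis covers these areas and could show them. What is missing is a stated regional PD-versus-control test.
- *That the gap carries through to Aim 2.* Aim 2 has a stated whole-brain analysis, its imaging expectation concerns a metabolic pattern, and the whole-brain resting-state fMRI analysis includes sensorimotor and cerebellar networks.
- *That the pilot already shows these increases.* It compared five PD patients who walked under DT with ten who rested during uptake. It had no controls and no single-task walking, so it speaks to neither Aim 1 contrast. It shows only that the authors have these areas in view.
- *That parietal regions must be added.* Table 1 has none, and the Motor and Gait Assessment section mentions "Cortical areas devoted to visual spatial ability such as the frontal and parietal lobes" as possibly susceptible in PD. No stated imaging prediction names a parietal region, so adding one is optional.

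It can also be said that comparing by region need not mean Table 1 alone. But the article names Table 1 as the list for PET in Aim 1 and offers no other regional definition. The mismatch therefore stands on what the article states, not on detail left to a fuller plan.

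**Conclusion.** The point holds in a limited form. The list fixed for the Aim 1 regional PET comparison contains 0 of 42 entries for the two territories predicted to be higher in PD, and at least 6 for the one predicted to be lower. The regional analysis as written can test the prefrontal half of the directional expectation and not the other half.

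This assumes that Table 1 is complete as printed and that the Aim 1 regional comparison uses it, as the article says. It does not imply that the general Objective 1 hypothesis, the pattern analysis or Aim 2 fails. The change is worth making because it is cheap and because its value depends on being made before the scans are analysed.

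**What to change.** Before any scan is analysed, do one of the following.

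1. Add left and right cerebellum and left and right sensorimotor cortex (precentral and postcentral) to Table 1. Name PFC, sensorimotor cortex and cerebellum as the prespecified Aim 1 set and treat the remaining entries as exploratory.
2. Keep Table 1 and state that this prediction is tested by a whole-brain PD-versus-control PET comparison, with its multiplicity correction named.

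Under the first option the table grows to 42 + 2 + 2 = 46 entries, or 42 + 2 + 4 = 48 if precentral and postcentral cortex are kept separate. Using the six entries labelled PFC, the prespecified set has 6 + 2 + 2 = 10 entries, or 6 + 4 + 2 = 12, so the short set more than offsets the extra comparisons. Parietal entries may be added if the authors want them.

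The cost is a table edit and a little more extraction from scans that are already planned. Recruitment, visits and image acquisition do not change.
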